## 7.5 Safety

(1) Indicators for safety evaluation

[1] Examinations for confirming recurrence

The investigator or the subinvestigator will perform imaging diagnosis by abdominal ultrasonography (US) and dynamic CT or dynamic MRI at 12-week intervals during the study drug administration period, as well as at the time of follow-up examination. If recurrence is suspected based on any other findings (such as gradual increase of tumor markers), imaging diagnosis by dynamic CT or dynamic MRI will be performed as needed.

[2] Other examinations for confirming recurrence

The investigator will precisely look for the recurrence of HCC by determining the levels of tumor markers during the study drug administration period. If recurrence is suspected by this determination, perform imaging diagnosis by dynamic CT or dynamic MRI as needed.

Tumor markers tests:

Determine AFP, AFP-L3 and PIVKA-II at 12-week intervals from the day of the start of study drug administration (within 14 days before the start) until the last day of study drug administration, and as well as at the time of follow-up examination.

If the study has been discontinued, AFP, AFP-L3 and PIVKA-II will be tested to the extent possible.

[3] Examinations related to the underlying disease

The investigator will perform HCV-RNA tests and fibrosis markers tests so as to examine the underlying disease during the study drug administration period.

1) HCV-RNA tests (quantitative)

Perform HCV-RNA tests at the time of registration (within 56 days before administration) and at 48-week intervals from the start of study drug administration until the end of study drug administration. Conduct genotype analysis on the day of the start of administration.

If the study is discontinued, perform HCV-RNA test to the extent possible.

2) Fibrosis markers tests

Perform hyaluronic acid test at 48-week intervals from the start of study drug administration (within 14 days before the start of administration) until the end of study drug administration.

If the study has been discontinued, hyaluronic acid will be tested to the extent possible.

[4] Medical examination

Examine symptoms and signs at 4-week intervals from the start of study drug administration (within 14 days before the start of administration) until the end of study drug administration, and at the time of follow-up examination.

If the study has been discontinued, symptoms and signs will be examined to the extent possible.

[5] Vital signs, etc.

Take body temperature (axillary), blood pressure (systolic/diastolic), pulse rate (dorsal position or sitting position) and body weight at 4-week intervals from the start of study drug administration (within 14 days before the start of administration) until the end of study drug administration, and at the time of follow-up examination.

If the study has been discontinued, body temperature (axillary), blood pressure (systolic/diastolic), pulse rate (dorsal position or sitting position) and body weight will be determined to the extent possible.

[6] Laboratory tests

Collect blood and urine samples and determine the following parameters at 4-week intervals from the start of study drug administration (within 14 days before the start of administration) until the end of study drug administration, and at the time of follow-up examination.

If the study has been discontinued, blood and urine samples will be collected and the following parameters will be determined to the extent possible.

1) Hematology tests: White blood cell count, red blood cell count, hemoglobin level, hematocrit, platelet count

2) Blood biochemistry tests: Total protein, serum albumin, serum bilirubin, total cholesterol, LDL cholesterol, HDL cholesterol, triglyceride, blood glucose, urea nitrogen, Cl, Na, K, Ca, ALP, AST (GOT), ALT (GPT), LDH, -GTP, choline esterase, serum creatinine, A/G ratio, free fatty acid, 2-microglobulin

3) Urinary tests (fresh urine): Qualitative (glucose, protein, urobilinogen, ketone body, occult blood), urinary albumin (converted to creatinine), urinary sediment (red blood cells, white blood cells, epithelial cells, casts, others), 2-microglobulin

[7] Blood pressure parameters

Collect blood and urine samples and determine the following parameters at 48-week intervals from the start of study drug administration until the end of study drug administration. If the systolic blood pressure exceeds 140 mmHg or the diastolic blood pressure exceeds 90 mmHg on two or more successive measurements, blood pressure parameters will be determined at the time of second or subsequent examination. However, determination of creatinine clearance, one of the blood pressure parameters, under increased blood pressure will be conducted to the extent possible.

1) Blood biochemistry tests: Renin activity, aldosterone, cortisol, uric acid, FT3, FT4, TSH, angiotensin II, hANP, BNP, catecholamine, growth hormone, dehydroepiandrosterone sufate (DHEAS)

2） Urinalyses (accumulated urine): creatinine clearance (if possible)

[8] Bone densitometry

Determine bone density of lumbar vertebrae (L2 to L4) with DXA before the start of study drug administration (period after radical therapy and before administration of the study drug) and at 48-week intervals until the day of the end of study drug administration.

If the study has been discontinued, bone density of lumbar vertebrae will be tested using DXA to the extent possible.

[9] Endoscopy

Conduct endoscopy of the stomach and esophagus before the start of study drug administration (period after radical therapy and before administration of the study drug) and at 48-week intervals until the day of the end of study drug administration.

If the study has been discontinued, endoscopy of the stomach and esophagus will be performed to the extent possible.

[10] ECG

Perform ECGs (12-lead) before the start of study drug administration (period after radical therapy and before administration of the study drug) and at 24-week intervals until the day of the end of study drug administration.

If the study has been discontinued, perform ECGs (12-lead) to the extent possible.

[11] Echocardiography

Perform echocardiography before the start of study drug administration (period after radical therapy and before administration of the study drug) and at 48-week intervals until the day of the end of study drug administration.

If the study has been discontinued, perform echocardiography to the extent possible.

[12] Pulse wave examination

Perform pulse wave examination before the start of study drug administration (period after radical therapy and before administration of the study drug) and at 48-week intervals until the day of the end of study drug administration.

If the study has been discontinued, perform pulse wave examinations to the extent possible.

[13] Fundus examination

Perform fundus examination before the start of study drug administration (period after radical therapy and before administration of the study drug) and at 48-week intervals until the day of the end of study drug administration.

If the study has been discontinued, perform fundus examination to the extent possible.

(2) Adverse events

Adverse events are defined as any unfavorable or unintended signs (including abnormal variations of laboratory test values), symptoms or diseases observed after administration of the study drug, irrespective of the causal relationship with the study drug concerned.

Recurrent HCC and other secondary cancers observed during the study period will be regarded as adverse events and analyzed separately from other adverse events.

If any adverse events have occurred, the following information will be recorded in detail. At that time, the severity of the symptom, outcome, causal relationship with the study drug, and comments will be assessed according to the standards presented below.

Adverse events for which causal relationship with the study drug cannot be definitely ruled out (causal relationship: 1 to 3) will be handled as adverse drug reactions.

[1] Name of adverse event

[2] Timing of onset and timing of outcome

[3] Degree of symptoms (severity: mild/moderate/severe; seriousness: not serious/serious)

[4] Study drug administration (continued/discontinued/completed)

[5] Whether treated or not

[6] Outcome (disappeared/remitted/unchanged/exacerbated/death/unknown)

[7] Causal relationship with the study drug (related/probab/related/possibly related/not related)

[8] Details about treatment and clinical course

[9] Details about causal relationship with the study drug

[Degree of symptoms]

| Severity | Mild | Easily bearable and not interfering with daily life |
| --- | --- | --- |
| Moderate | Interfering with usual activities |
| Severe | Disabling usual activities |
| Seriousness | Not serious | Adverse events other than serious adverse events |
| Serious | Serious adverse events (See 9.3 Reporting adverse events) |

[Outcome ]

| 1 | Disappeared | Symptoms/signs have disappeared, and test values have become normal or recovered to the pre-administration levels. |
| --- | --- | --- |
| 2 | Remitted | The severity has decreased or symptoms/signs have shown a tendency toward improvement. |
| 3 | Unchanged | There are no changes in symptoms · signs and test values. |
| 4 | Exacerbated | Symptoms/signs and test values have become exacerbated. |
| 5 | Death | The patient died. |
| 6 | Unknown | Symptoms/signs or test values are unknown because the patient did not show up, etc. |

[Causal relationship with the study drug]

| 1 | Related | Clinical symptoms including abnormal laboratory test results have occurred at a temporally reasonable timing in relation to the study drug administration, and cannot be explained by concurrent diseases or other concomitant drugs or chemical substances. Clinically plausible responses are seen after discontinuation (interruption) of study drug administration. The symptoms can be reproduced pharmacologically or phenomenologically definitely by reasonable re-administration, if necessary. |
| --- | --- | --- |
| 2 | Probably Related | Clinical symptoms including abnormal laboratory test results have occurred at a temporally reasonable timing in relation to study drug administration, and their association with concurrent diseases or other concomitant drugs or chemical substances can probably be ruled out. A clinically reasonable response is observed after discontinuation (interruption) of study drug administration. Information regarding re-administration is not required for this definition. |
| 3 | Possibly related | Clinical symptoms including abnormal laboratory test results have occurred at a temporally reasonable timing in relation to study drug administration, and can be explained by concurrent disease or other concomitant drugs or chemical substances. Information regarding discontinuation of study drug administration is not available or unclear. |
| 4 | Not related | Definite factors other than the study drug (such as physiological factors, environmental factors, restraints, exercise, measurement errors, etc.) are present, and the absence of causal relationship with the study drug can be reasonably explained with sufficient information. |

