| Cheilitis | 0 | 2 | 6 | 8 | 4.4 |
| Dry lip | 0 | 0 | 4 | 4 | 2.2 |
| Itching | 0 | 0 | 3 | 3 | 1.6 |
| Folliculitis | 0 | 1 | 0 | 1 | 0.5 |
| Plantar fissure | 0 | 0 | 1 | 1 | 0.5 |
| Nail fragility | 0 | 0 | 1 | 1 | 0.5 |
| Flickering feeling in the eyes | 0 | 0 | 1 | 1 | 0.5 |
| Itchy sensation of eyelids | 0 | 0 | 1 | 1 | 0.5 |
| Foreign body feeling of oesophagus | 0 | 0 | 1 | 1 | 0.5 |
| Stomach discomfort | 0 | 0 | 1 | 1 | 0.5 |
| Diarrhoea | 0 | 0 | 1 | 1 | 0.5 |
| Queasy | 0 | 0 | 1 | 1 | 0.5 |
| Burning sensation in face | 0 | 1 | 0 | 1 | 0.5 |
| Malaise in whole body | 0 | 1 | 0 | 1 | 0.5 |

Abnormal laboratory test values in a clinical study in patients with skin diseases 12)

| Parameter | Total number of events | Frequency (%) |
| --- | --- | --- |
| Transient increase of TG | 2 | 1.1 |

(2) Potential risks in this study

In this study, liver biopsy will be performed for determination of the liver gene expression profile and drug concentrations. Risks of complications associated with liver biopsy such as haemorrhage (haemorrhage from the liver surface at the puncture site), infection, pneumothorax (it can be induced if the lung is injured during the puncturing process), and shock (it can be caused by incompatibility with anesthesia) cannot be completely ruled out, although the likelihood is extremely small. Therefore, the operation should be performed with measures of precaution, including careful preliminary examination.

(3) Benefits for subjects

In non-clinical studies, oral administration of the doses of 40 mg/kg or more significantly inhibited hepatocarcinogenesis in rats induced by 3'-MeDAB and DEN15).

Muto et al. reported that in their clinical study of E-5166, a substance identical to NIK-333, a daily dose of 600 mg administered for 1 year to patients who received treatment for primary HCC significantly inhibited recurrent HCC, as compared with the placebo group,13) and improved the survival rate.14)

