## 4.7 Amount of liver tissue samples collected and frequency of sample collection

Perform liver biopsy and collect liver tissues on the day before the start of study drug administration and at Week 8 of study drug administration. Collect about 40 mg of liver tissue sample in one procedure of liver biopsy and a total of about 80 mg of tissue.

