| Echocardiography | |  |  |  |  |  |  |  |  |  |  |
| Pulse wave examination | |  |  |  |  |  |  |  |  |  |  |
| Fundus examination | |  |  |  |  |  |  |  |  |  |  |
| Adverse events | |  |  | | | | | | | |  |

: The day before the start of administration and the day of evaluation at Week 8

: Examination will be conducted during the period between the end of radical therapy and the start of study drug administration.

: Examination will be conducted at 48-week intervals.

: Examination will be conducted upon discontinuation of the study if possible.

Note 1: The acceptable range of deviation from the scheduled examination, observation and evaluation during the study period is +28 days for gene expression profile (Week 8) and pharmacokinetics (Week 8); 35 days for abdominal imaging diagnosis, HCV-RNA, HCG tests, tumor markers, fibrosis markers, bone densitometry, endoscopy, ECG, echocardiography，pulse wave examination, and fundus examination; and 7 days for other parameters.

Note 2: Subjects need to be hospitalized on the day of the start of administration and on the day of evaluation at Week 8. Liver biopsy will be performed and blood samples and accumulated urine samples will be collected on the day before the start of administration, with administration of the study drug to start 24 hours after the operation. On the day of evaluation at Week 8, subjects will visit the hospital without taking the study drug, and undergo liver biopsy 4 hours after administration. Blood samples will be collected 4 and 8 hours after administration. Urine samples will be accumulated for 24 hours after administration.

Note 3: Blood pressure parameters will be assessed on the day of the start of administration and at Week 48 and Week 96 of administration. If the systolic blood pressure exceeds 140 mmHg or the diastolic blood pressure exceeds 90 mmHg in two or more consecutive tests, the parameters will be determined on the second or subsequent tests. Determination of creatinine clearance, one of the blood pressure parameters, under increased blood pressure will be conducted to the extent possible. Creatinine clearance will be determined using urine samples collected at home at the timings other than the day of the start of administration (i.e., Week 48 and Week 96 of administration, and examination of blood pressure parameters in the presence of increased blood pressure).

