## 9.3 Reporting of adverse events

The investigator or the subinvestigator will report all adverse events encountered to the sponsor. Immediately report the emergence of any serious adverse events listed below to the head of the study center and the sponsor by telephone or fax irrespective of the causal relationship with the study drug. After that, the investigator will immediately report the events to the head of the study center and the sponsor in writing. When additional information has been requested by the head of the study center and the sponsor, the investigator will provide such information.

[Serious adverse events]

[1] Resulting in death

[2] Life-threatening

[3] Requiring inpatient hospitalization or prolongation of existing hospitalization for treatment

[4] Resulting in persistent or significant disability/incapacity

[5] Leading to a congenital anomaly

[6] Other medically important states

The adverse events listed above include those attributable to adverse reactions to the study drug, or to infections which are suspected to be attributable to the use of the study drug.

[Emergency safety center]

Bellsystem 24, Inc.

[contact] [contact]

Reception hours: Around the clock (24 hours)

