[1] Cases of deviation after registration

- Subjects for whom safety data are not available

- Subjects who have not taken the study drug at all

(3) Pharmacokinetics

The “Pharmacokinetics Analysis Set” is obtained by eliminating the following subjects from among the registered subjects.

[1] Cases of deviation after registration

- Subjects for whom pharmacokinetics data are not available

- Subjects who have not taken the study drug at all

(4) Plasma TGF-

The “Plasma TGF- Analysis Set” is obtained by eliminating the following subjects from among the registered subjects.

[1] Cases of deviation after registration

- Subjects for whom the data of TGF- concentrations in plasma are not available

- Subjects who have not taken the study drug at all

(5) Handling of missing data

If any values of vital signs, hematology tests, blood biochemistry tests, urinary tests, bone densitometry, endoscopy, ECG, echocardiography, pulse wave examination or fundus examination are missing because the examination or determination has not been conducted or for other reasons, the data will be handled as missing data.

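### The adverse-event window opens only after the first dose, so a complication of the baseline research biopsy seen only before dosing has no reporting route and is not tabulated

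*Protocol*

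**What the plan says.** **Definition.** Protocol section 7.5 (2) covers unwanted signs (abnormal laboratory changes included), "symptoms or diseases observed after administration of the study drug, irrespective of the causal relationship with the study drug concerned". It gives no starting point at consent, registration or first study procedure.

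**Timing of the biopsy.** Section 4.7 instructs: "Perform liver biopsy and collect liver tissues on the day before the start of study drug administration and at Week 8 of study drug administration". Note 2 to the study schedule in section 7.3 repeats the baseline timing ("Liver biopsy will be performed and blood samples and accumulated urine samples will be collected on the day before the start of administration") and sets the interval: "with administration of the study drug to start 24 hours after the operation". Section 7.4 (1) gives the purpose as measuring liver gene expression and liver drug concentration, so the biopsy is done for research.

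**Recognised risk.** Section 2.4 (2), on risks of taking part in this study, refers to "Risks of complications associated with liver biopsy such as haemorrhage (haemorrhage from the liver surface at the puncture site), infection, pneumothorax" and also to shock. It calls the likelihood extremely small and gives no rate.

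**Reporting.** Section 9.3 states: "The investigator or the subinvestigator will report all adverse events encountered to the sponsor". Immediate notification of the sponsor and the head of the centre applies to serious adverse events, so both duties depend on the 7.5 definition.

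**Analysis.** Section 12.3 lists and tabulates adverse events, and summarises laboratory and other scheduled observations. The Safety Analysis Set in section 12.7 (2) starts from registered subjects and removes, among others, "Subjects who have not taken the study drug at all".

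**The concern.** The protocol requires an invasive research procedure before any drug is given, names its risks, and then defines reportable events so that they begin only after drug is given. A bleed a few hours after the baseline biopsy that prolongs the hospital stay would meet a seriousness criterion in 9.3. It would still not be an adverse event if it resolved before dosing or if dosing never began.

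What is at stake is mainly subject protection. In a 12-subject study the sponsor would want to know of a serious biopsy complication before the next subject has the same procedure, and the text does not require anyone to say so. The study report could also be silent on a harm caused by taking part.

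**Working it through.** No planned figure bears on this point, so there is none to reproduce. The check is mostly a reading of the sections against one another.

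**Which biopsy complications fall within the definition?** The wording turns on when a sign is observed, not on when it began.

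| Complication | Adverse event under 7.5 (2)? | Reportable under 9.3? | Tabulated under 12.3? | Subject in Safety Analysis Set? |
|---|---|---|---|---|
| Baseline biopsy; observed and resolved before first dose; subject then dosed | No | No | No | Yes, without the event |
| Baseline biopsy; subject never dosed | No | No | No | No |
| Baseline biopsy; still present after first dose | Yes | Yes | Yes | Yes |
| Baseline biopsy; first observed after first dose (for example a later infection or delayed bleed) | Yes | Yes | Yes | Yes |
| Week 8 biopsy | Yes | Yes | Yes | Yes |

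The first two rows are the gap.

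**Does another section close it?**
- Section 8.2 has subjects tell the investigator of abnormalities. It requires no onward report to the sponsor.
- Section 7.3 records complications as subject background, alongside previous history. That is not event reporting.
- Section 8.3 has the case report form record the reasons, details, treatment and course of a discontinuation. Section 10.2 adds follow-up where a subject stops for a safety problem. The section 7.3 flow puts registration and assignment before the biopsy, so a subject too ill to start is already registered and could be documented this way, but with no immediate reporting and outside the safety tables. A subject who recovers and is dosed does not reach these sections.
- Section 17.2 makes the sponsor responsible for compensating injury caused by the study, but creates no duty to report it.

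**Number of procedures involved.** Sections 12.6 and 4.7 give 12 subjects × 2 biopsies = 24. Of these, 12 precede any dose and 12 follow it. The 12 counts procedures that have an uncovered interval of about 24 hours; it does not count lost events.

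**Chance that it matters in this study.** The documents give no complication rate, so the per-biopsy rates p below are assumptions. For 12 independent baseline biopsies, P(at least one complication) = 1 − (1 − p)^12:
- p = 0.1%: 1 − 0.999^12 = 1.2%
- p = 1%: 1 − 0.99^12 = 11.4%
- p = 2%: 1 − 0.98^12 = 21.5%
- p = 5%: 1 − 0.95^12 = 46.0%

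These are upper limits for the gap at each rate, because complications that persist or appear after dosing are covered. The finding does not depend on them.

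**The case against.** The strongest reply is that the study's safety objective concerns NIK-333, with a cardiovascular focus. Causality is judged against the drug, and a dosed-only safety set suits that purpose. Much of this stands: the dosed set is right for the drug-safety tables and should stay. It does not explain why harm from a required research procedure has no route to the sponsor.

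It can also be said that the worst case, a subject too ill to start drug, would be documented under 8.3 and 10.2. That is a fair reading and limits the point. Those records are neither immediate nor tabulated, and they miss the subject who recovers and is dosed. The Step I case report form and its completion guidance are not shown, so a field for biopsy complications may exist. A field alone would not bring such events under 9.3.

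A reader might draw four stronger conclusions, which the documents do not support:
- **Half of the biopsies go unmonitored.** Section 7.4 (1) requires a prior bleeding-risk check, ultrasound guidance, rest and hospitalisation, and this applies at both biopsies. The gap is in recording and reporting.
- **Every complication in the first 24 hours is lost.** Any that persists past the first dose is observed after administration and qualifies.
- **A reported biopsy-complication rate is biased downward.** The protocol plans no such rate.
- **Bleeds will be attributed to the drug.** Section 7.5 (2) records time of onset and the reasoning on causality, and offers a not-related category for definite other causes.

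**Conclusion.** The point holds in a narrow form. Followed exactly, the protocol leaves a baseline-biopsy complication outside 9.3 reporting and outside the safety tables if it is observed only in the roughly 24 hours before the first dose, or if the subject is never dosed. In the second case the subject also leaves the Safety Analysis Set. At most 12 procedures are affected, and the protocol regards complications as very unlikely. No planned estimate changes.

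This rests on a literal reading of the definition and on no other document bringing pre-dose events into 9.3. It is worth correcting because it concerns subject safety and the correction costs little.

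**What to change.** 1. In section 7.5 (2), open the adverse-event window at informed consent or at the start of the baseline biopsy, and flag each event as before or after first dose.
2. In section 9.3, state that serious events before the first dose are reportable on the same terms.
3. In sections 12.3 and 12.7 (2), add a separate listing of pre-dose events that includes biopsied but never-dosed subjects. Keep the dosed Safety Analysis Set for the drug-safety tables.

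The cost is a revised definition, a before/after-dose flag, one short listing and a few more listed events. The drug-safety analysis is unaffected.

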Adverse events of particular clinical significance were not observed at Level 1 (300 mg group) and Level 2 (600 mg group), and tolerability was judged to have been confirmed. However, the gastric polyp observed at Level 1 was considered an event requiring endoscopic exam in the subsequent phases.

At Level 3 (900 mg group), blood pressure increase was observed in 4 out of 9 subjects during the period of 24 weeks from the start of repeated administration. Since this event was an unknown adverse reaction, and the mechanism of its onset has not been understood, administration of the study drug and enrollment of new subjects were discontinued. Although the symptom related to the event disappeared after pharmacotherapy, the extent shifted from the normal range to the range of severe hypertension in some subjects, prompting the event to be regarded as an important event that could have accompanying secondary inconveniences unless some treatment was given. Moreover, some subjects exhibited protein urine and urinary occult blood in association with blood pressure increase, and some subjects exhibited abnormal changes in protein urine and urinary occult blood without blood pressure increase. The frequency of the occurrence of abnormal changes in urinary qualitative parameters was high at Level 3. Furthermore, nail disorder, which is known to be induced by taking a large amount of retinoid, was seen in 2 subjects about 12 weeks after the end of administration. For these reasons, 900 mg was deemed inappropriate as a clinical dose.

The effect of NIK-333 on bone, which was seen in non-clinical studies, was not observed at any of the levels assessed.

2) Pharmacokinetics

There were no differences in the plasma concentrations of unchanged NIK-333 in the fed and fasted conditions.

The pharmacokinetic parameters (AUC0-24hr and Cmax) of unchanged NIK-333 in plasma were confirmed to exhibit linearity after single or repeated administration of 300 mg, 600 mg and 900 mg.

Since almost no unchanged NIK-333 and NIK-333 lipids form were seen in plasma at Week 48 of administration and Week 12 and Week 24 after the end of administration, the drug was not considered to be accumulated in the body during repeated administration.

Excretion of unchanged NIK-333 in urine was not seen after single administration.

3) Conclusions

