## 12.3 Safety analysis

Prepare tabulated lists of adverse events (symptoms and signs, etc.), and tabulate the data by type and severity. Concerning laboratory tests, prepare tabulated lists and time-course charts, and calculate summary statistics. Tabulate other observation parameters in the same way as laboratory tests.

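### The severity scale in section 7.5(2) is purely functional, so a silent blood pressure, urinary, laboratory, bone density or fundus change can only be graded mild, whatever its size

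*Protocol*

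**What the plan says.** Section 7.5(2) of the protocol defines adverse events as "any unfavorable or unintended signs (including abnormal variations of laboratory test values), symptoms or diseases observed after administration of the study drug", whatever their cause. For each event the severity, outcome and causal relationship "will be assessed according to the standards presented below". The severity standard printed there has three levels:

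- mild: "Easily bearable and not interfering with daily life"
- moderate: "Interfering with usual activities"
- severe: "Disabling usual activities"

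Seriousness is a separate item, defined in section 9.3.

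Section 12.3 gives the analysis: "Prepare tabulated lists of adverse events (symptoms and signs, etc.), and tabulate the data by type and severity". It goes on to require lists, time-course charts and summary statistics for laboratory tests, and the same handling for the other observation parameters.

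Section 3 puts the safety focus of the long-term phase on the cardiovascular system. The Step II rationale in section 4.4(3) adds the urinary system and cites the blood pressure effect seen at 900 mg/day.

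**The concern.** Most of the scheduled safety measurements can change a great deal without the patient noticing: blood pressure, urine protein and occult blood, blood chemistry, bone density and fundus photographs. These are the measurements through which Step II looks for harm. A scale that asks only whether daily life is disturbed gives one grade to a marginal and to a very large silent change.

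The protocol's account of phase I in section 2.3 shows that size mattered to the sponsor. For blood pressure at 900 mg it notes that "the extent shifted from the normal range to the range of severe hypertension in some subjects", and it tabulates urinary changes by the number of grades shifted from baseline. The severity scale for this trial cannot express either distinction.

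At stake is whether the by-severity adverse event table says anything useful about the organ systems it is most needed for.

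**Working it through.** There is no calculation to reproduce: the point rests on a definition, and section 12.6 justifies the 12 subjects by feasibility alone. The check is a side-by-side reading.

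1. **Which events are graded.** The definition in 7.5(2) includes signs and abnormal laboratory variations, so an asymptomatic finding reported as an adverse event must receive a severity grade.

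2. **Which standard applies.** Section 7.5(2) refers to the standards printed there. The only severity standard is the three-level functional one. No level depends on a measured value, a shift from baseline or a need for treatment, and no external toxicity scale is named.

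3. **Applying it.** Moderate and severe both need an effect on usual activities. An event with no such effect meets neither definition. Mild is all that remains, at any size of change.

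4. **Comparison with the neighbouring scales.** The outcome scale speaks of test values returning to normal or to pre-administration levels. The causality scale speaks of abnormal laboratory results. Only the severity scale leaves test values out, although it grades the same events. This looks like an oversight rather than a choice.

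5. **Is a magnitude rule given elsewhere?**
   - Section 7.5(1)[7] uses 140/90 mmHg, exceeded on two or more successive measurements, to trigger additional tests. It assigns no grade.
   - Section 5.3[5] uses 160/100 mmHg as an entry limit. It assigns no grade.
   - The urinary shift grades in section 2.3 describe phase I results and are not a rule for this trial.
   - Tables 1 to 3 list the tests without grading them.
   - Section 21.2 points to separate guidance on completing the case report forms. It is not at hand, and 7.5(2) does not refer to it for severity.

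6. **How the grade reaches the results.** Under section 13.2, severity entered directly on the case report form counts as source data. Section 12.3 then uses severity as one of the two axes of the adverse event tabulation.

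7. **What is preserved outside that table.** The rest of 12.3 covers the measured values. Section 7.5(2) also records seriousness, whether the event was treated, whether study drug was continued, and the clinical course. Section 9.3 includes other medically important states among the serious events.

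Steps 1 to 6 establish the defect in the grade and its table. Step 7 limits its reach.

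**The case against.** The strongest reply is that section 12.3 must be read whole. The size of each numerical change will be listed, charted and summarised, in about 12 subjects, where individual values can be inspected. A large silent rise in blood pressure can also be classed as serious, and its treatment is recorded. This stands. A reader might infer that the plan would lead to a false conclusion of good long-term safety at 600 mg/day. The documents do not support that, because such a conclusion would require ignoring these other outputs.

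A reader might also infer that the phase I blood pressure events would all have been graded mild here. That is not shown either:

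- The 4 of 9 subjects with a blood pressure increase received 900 mg, a dose not given in this trial. At 600 mg the repeated-dose table lists one related event.
- Section 2.3 mentions a symptom that resolved after drug treatment, and the 900 mg list includes 6 related headaches, so absence of symptoms is not documented.
- Section 2.3 rests the importance of the event partly on what might follow without treatment, which is closer to seriousness than to severity.
- The urinary shifts in phase I were reported in a table of their own, apart from the adverse event list.

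These points weaken any claim about consequences. They do not change what the scale says. Seriousness is a separate yes-or-no judgement and leaves the severity grade as it was. Fundus and endoscopy findings do not reduce naturally to summary statistics, so the severity grade matters more for them. An investigator might depart from the printed scale, but nothing in the protocol provides for it, and unguided departures would make grades inconsistent. Nor is this a detail left to a statistical analysis plan: the protocol fixes the scale, and the investigator applies it when the event is recorded.

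**Conclusion.** The point holds for the severity grade and the table built on it. As written, section 7.5(2) places every silent sign or abnormal test value in the mild category regardless of size, and the by-severity table in 12.3 therefore cannot distinguish small from large changes of this kind in the cardiovascular and urinary systems.

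The effect cannot be given as a number. The documents do not say how many events would be asymptomatic, and no rate of events by severity serves as an endpoint or decision rule. The conclusion assumes that investigators follow the printed definitions and that the unseen form guidance adds no further rule. The size of numerical changes is kept elsewhere in the analysis, so this is a worthwhile, inexpensive improvement and not a threat to the safety assessment as a whole.

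**What to change.** In section 7.5(2), keep the functional scale for symptoms. For signs and test values, add or name a prespecified magnitude-based severity scale covering blood pressure, urinary findings, laboratory values, bone density and fundus findings. The sponsor should choose the thresholds. The 140/90 and 160/100 mmHg values already in the protocol should not be taken over as severity bands by default, since they were set for other purposes. In section 12.3, show the magnitude-based grade beside the functional grade and do not merge the two, so that each keeps its meaning.

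The cost is one more table in the protocol and matching guidance for the case report form. No new measurements are needed, because all of these examinations are already scheduled. The downside is that more events will be graded moderate or severe.
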